#### Youth Offending

The Youth Justice dataset was provided by the NT Department of the Attorney-General and Justice, and this contains records of youth offending in the NT. The outcome measure for this study will be the cumulative incidence of first episode of a proven guilty offence within the youth justice system. The starting point for follow-up will be the 10th birthday, which is the minimum legal age of criminal responsibility, and the follow-up time will be calculated to the date of first offence or censored at the date of death, the last observed date in the linked datasets, or the set endpoint for follow-up of this study. Data are available for the period 1997 to 2017.

### Control Variables

The selection of control variables will vary between studies and the availability of the relevant variables in the linked datasets. We will draw reference from published literature in selecting control variables known to have confounding or moderating effects on the association being investigated. Individual-level control variables will be retrieved from the linked health, education, child protection, and justice datasets, including maternal and perinatal factors from the Perinatal Registry dataset (a statutory collection containing information for all births in the NT), as well as hospital admission diagnoses from the NT Hospital Separation Dataset. Community-level factors will include relative level of geographic remoteness (as measured with ARIA+), housing crowdedness (as measured with average household size and average persons per bedroom in the community), and socioeconomic disadvantage (as measured with the Index of Relative Socio-Economic Disadvantage) [48,50,64]. Aggregated data on these factors will be combined with the linked administrative datasets, using the relevant location variable for each study (either community of residence or school location).

### Statistical Analysis Plan

For each component study, statistical analyses will start with descriptive statistics to examine the distribution of key demographic, control, predictor, and outcome variables in the study cohort. The approach of complete-case analysis will be adopted in regression analysis. As this approach may lead to exclusion of participants with missing data, we will include comparisons of the study cohort and those excluded from analysis using suitable statistical methods (z-test, *t* test or chi-square analysis) to assess the differences between the 2 groups. When the groups are found to be statistically different on any number of included variables, we will include discussion of the implications of these differences on the validity of the study’s findings.

The dependent variable, HI, is structured as an ordinal variable, and we anticipate a *dose-response* relationship between the levels of HI and the outcome variables. In all regression analyses, the investigation of associations will use *normal hearing* as the reference category.

The study investigating the impact on AEDC outcomes will use logistic regression for dichotomous outcomes and linear regression on continuous ones. In the studies investigating the impact of HI on Year 1 attendance rates and NAPLAN results, multivariate linear regression models will be fitted to estimate the association between HI and the school-based outcome measures, and the models will include school-fixed effects to control for the average observed and unobserved differences in schools and students of the schools. In the studies examining the association between HI and child maltreatment and between HI and youth offending, multivariate survival analysis will be used by fitting Cox proportional hazard models.

In these component studies, a parsimonious model building strategy will be adopted in the regression modeling process. Univariate regression analysis will first be carried out to select variables with *P* value<.25. These and all possible 2-way interaction terms will be fitted in the multivariate regression model–building process. Variables deemed to be key confounders or moderators selected on the basis of past studies will be retained throughout the model-building process.

The final part of the study will investigate the interplay of key early childhood factors known to be associated with youth offending. It will examine how and to what extent the outcome of youth offending in NT Aboriginal children is shaped by the health, developmental, educational, and social factors investigated in this study, including HI, AEDC outcomes, Year 1 attendance rates, Year 3 NAPLAN results, and child maltreatment. The analysis will also examine the influence from key demographic factors relevant to children’s family and school learning circumstances. Structural equation modeling (SEM), using path analysis methods, will be utilized to quantify the relative impact of these factors on the outcome of youth offending. Distributional assumptions will be assessed to identify any outliners. The model will examine the direct pathway through which HI is associated with youth offending; it will also include the indirect pathways by which AEDC outcomes, Year 1 school attendance, and Year 3 NAPLAN results act as mediators in the direct pathway. In the SEM analysis, the *maximum likelihood with missing values* convergence method will be used to relax the requirement for each child to have complete data, as it is expected that the number of children will be reduced after linking multiple datasets. Relevant model fit indices will be reported for each pathway, including *P* value, model chi-square, goodness of fit index, p of close fit, comparative fit index, the root-mean-squared error of approximation, and the standardized root mean square residual. All statistical analyses will be performed using Stata for Windows, Version 15 (StataCorp).

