### Objectives

To address this research gap, the Hearing Loss in Kids (HeLoKids) Project aims to apply a life-course epidemiological approach [45] to investigate the association between HI and developmental, educational, and social outcomes in Aboriginal children living in remote Northern Territory (NT) communities. By using linked administrative datasets containing longitudinal unit-record data for health, education, child protection, and youth justice systems, as well as hearing assessment results, this study is able to examine the selected outcomes while controlling for a wide range of potential confounders and moderators, as illustrated in the conceptual model in Figure 1.

Specifically, the study will undertake a series of studies that test the following hypotheses:

HI is independently associated with poorer developmental outcomes at the time of entry into full-time school (aged about 5 years).HI is independently associated with lower school attendance rates in Year 1 (aged about 6-7 years).HI is independently associated with poorer academic achievements in Year 3 (aged about 8 years).HI is independently associated with higher risk of child maltreatment.HI is independently associated with higher risk of youth offending.

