### The Study Cohort

The study cohort comprises NT-born Aboriginal children, with hearing assessment results in the RHA dataset and with a residential location classified as *remote* or *very remote* on the basis of ARIA+ [48]. Further inclusion and exclusion criteria will vary among the component studies of this study, depending on the respective requirements. In principle, as the data analysis will be based on a complete-case analysis, only children with data in the selected dependent, outcome, and control variables will be included. Children who have had surgical treatment for OM before the age of 4 years will be excluded, as the surgery could alter the impact of HI during the early childhood period. This will be done by searching in another linked administrative dataset, the NT Hospital Separations Dataset, and excluding children admitted before the age of 4 years, with any diagnosis code plus any procedure code related to OM and its treatment (Table 1).

**Table 1 table1:** Otitis media—related hospital admission diagnoses and surgical procedures used to exclude children who had received surgical treatment, with International Classification, 10th Revision-Australian Modification codes.

ICD-10AM^a^ Code		Diagnosis/procedure

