#### Academic Performance in Year 3 of Primary School

The outcome measure for children’s academic performance in early years of primary school will be taken from the National Assessment Program–Literacy and Numeracy (NAPLAN) dataset. NAPLAN is an annual national assessment program, which commenced in 2008, and is undertaken by all students in Australia in years 3, 5, 7, and 9 (aged approximately 8, 10, 12, and 14 years, respectively) [62]. NAPLAN includes separate tests for numeracy, reading, writing, and language conventions (which include spelling, grammar, and punctuation). The test contents are developed to include specific considerations for Indigenous education, English as a second language, and special needs education [63]. The tests are designed to assess students’ understanding of the core elements of the national curriculum and to assist schools and teachers to identify students who may not have learned the skills required to progress academically. The raw score for each test is converted into a scaled score out of 1000. Data were available from 2008 to 2016. The outcome measures for this study will be the scale scores for the 5 NAPLAN domains for Year 3. The selection of Year 3 optimizes the study cohort by avoiding both the declining school attendance and declining participation in NAPLAN assessments in later years.

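### Complete-case analysis is the only method named for the component regressions, and for Year 3 NAPLAN it may pull the hearing-impairment effect toward the null

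*Protocol article*

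**What the plan says.** The Statistical Analysis Plan section of the protocol article sets the missing-data method for the component regressions: "The approach of complete-case analysis will be adopted in regression analysis". The Study Cohort section builds it into eligibility: "only children with data in the selected dependent, outcome, and control variables will be included". (In this article the word dependent refers to the hearing variable.)

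Two steps deal with the children who are lost. The Statistical Analysis Plan says "we will include comparisons of the study cohort and those excluded from analysis using suitable statistical methods", meaning z, t or chi-square tests. Where a test finds a difference, "we will include discussion of the implications of these differences on the validity". The Principal Findings section lists complete-case analysis among the possible sources of bias and promises to discuss likely direction and extent.

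Three other statements matter:

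- Objectives, hypotheses 2 and 3: "HI is independently associated with lower school attendance rates in Year 1" and "HI is independently associated with poorer academic achievements in Year 3".
- The section on Year 3 academic performance says that year was selected with a view to "avoiding both the declining school attendance and declining participation in NAPLAN assessments in later years".
- For the structural equation model (SEM), a maximum-likelihood "convergence method will be used to relax the requirement for each child to have complete data".

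**The concern.** Complete-case regression of NAPLAN score on HI uses only children who sat the test. If attendance affects both sitting and the score, and HI lowers attendance, the sitters with HI are selected more strongly for good attendance than the sitters without HI. The gap in attendance between the groups shrinks among sitters, and the part of the HI effect that runs through attendance shrinks with it. A policy-relevant effect would then be reported as too small.

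The planned safeguard cannot measure this. A P value depends on group size as well as on the difference, so it is a poor trigger for discussion. Children without a NAPLAN score cannot be compared on the score at all. Putting attendance into the regression as a control would not solve it either: the article's own path model treats attendance as a mediator, so adjusting for it removes part of the effect of interest. Weighting or imputation can use attendance without that cost.

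**Working it through.** The article gives no missing rate, effect size or attendance-score correlation, so there is no planned figure to reproduce. Every input below is an assumption.

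**Model.** H = 1 for HI. Attendance A = −a·H + noise (SD 1). Score Y = −d·H + b·A + noise. Log-odds of sitting = g0 + gA·A − gH·H.

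**Formulas.**

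- Full-data HI effect = −(d + a·b)
- Complete-case HI effect = −d + b·D, where D = mean attendance of sitters with HI minus mean attendance of sitters without HI (by numerical integration)
- Attenuation = 1 − complete-case effect / full-data effect

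**1. Attendance alone drives sitting** (a = 0.3, b = 0.5, g0 = 1, gH = 0; 63% to 71% sit).

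| gA | D | Complete-case, d = 0.1 (full −0.250) | Attenuation | Complete-case, d = 0 (full −0.150) | Attenuation |
|---|---|---|---|---|---|
| 0.5 | −0.2862 | −0.2431 | 3% | −0.1431 | 5% |
| 1.0 | −0.2560 | −0.2280 | 9% | −0.1280 | 15% |
| 1.5 | −0.2252 | −0.2126 | 15% | −0.1126 | 25% |

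Example, gA = 1.0 and d = 0.1: −0.1 + 0.5 × (−0.2560) = −0.2280, and 1 − 0.2280/0.250 = 8.8%. The 25% is reached only when HI has no direct effect on the score.

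**2. Other mechanisms** (a = 0.2, b = 0.5, d = 0.1; full-data effect −0.200).

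| Sitting depends on | gA, gH, g0 | Sit, HI v no HI | D | Complete-case | Attenuation |
|---|---|---|---|---|---|
| HI only | 0, 0.5, 1 | 62% v 73% | −0.2000 | −0.2000 | 0% |
| Attendance, high participation | 1, 0, 2.5 | 88% v 90% | −0.1847 | −0.1923 | 4% |
| Attendance and HI | 1, 0.5, 1 | 56% v 70% | −0.0925 | −0.1463 | 27% |
| Attendance (strong) and HI | 2, 0.5, 0.5 | 44% v 58% | −0.0361 | −0.1180 | 41% |

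Missingness that depends on HI alone does no harm, because HI is in the model.

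**3. What weighting recovers.** In simulations of 1,000,000 children per scenario with the part 2 inputs and variants of them (Monte Carlo error about 1% of the effect), inverse-probability weights from attendance and HI came within 5% of the full-data effect whenever sitting depended only on those two. When sitting depended on the score itself, complete-case attenuation was 13%, and 29% with attendance added. Weighting left 10% and 21%.

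**Limits.** The model has no school fixed effects and no controls. The planned regression has both, so a, b and gA should be read as within-school quantities after adjustment, and these may be smaller.

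**The case against.** The strongest reply is that the authors have seen the issue. They name complete-case analysis as a source of bias, promise to discuss direction and extent, and chose Year 3 partly because participation falls later. This is a real design mitigation and deserves credit. It does not show that Year 3 participation is near complete, and discussion cannot put a number on the bias.

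Several stronger readings are tempting, and the article does not support them.

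- *The hypotheses themselves link missing data to HI and attendance.* They link HI to attendance and to scores. The step to not sitting NAPLAN is an inference, made plausible because the article mentions attendance and participation together.
- *The estimates are biased.* They may be. The bias is nil if sitting depends only on HI or on variables in the model, and small if few children are missing or the attendance link is weak.
- *The plan contradicts itself because the SEM uses a likelihood method, and linked data go unused.* The article gives a reason: the SEM needs many datasets jointly, which reduces numbers. Each component study needs one outcome. The difference is a choice, and the SEM does use partial records. It remains true that the HI-to-NAPLAN relation will be handled in two ways.
- *All five studies are equally exposed.* The maltreatment and offending outcomes come from administrative records with censoring, so loss there arises mainly through covariates. The Perinatal Registry covers all NT births and the cohort is NT-born, so nothing shows that covariate loss is material.
- *Missing at random is simply a weaker assumption.* The two assumptions are not nested. Complete-case regression stays valid when missingness depends on unseen covariate values, where standard imputation can fail.

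**Conclusion.** The point holds as a limited one. Complete-case analysis is a stated choice for the component regressions, backed only by significance tests and discussion. For Year 3 NAPLAN it may attenuate the HI effect.

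The size cannot be computed from the article. Under the assumed inputs it runs from near 0 to about 25% when attendance alone drives sitting, and was 27% and 41% in the two scenarios where HI also drives it. These figures show direction and possible scale and are not forecasts. They rest on HI lowering attendance, on attendance raising both the score and the chance of sitting, and on appreciable non-participation in Year 3. A reader should not infer that bias is certain or that it applies equally to the other four outcomes.

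**What to change.** 1. For NAPLAN, define the denominator as cohort children enrolled in Year 3 in NT Government schools, since the attendance dataset covers only those schools. Prespecify inverse-probability-of-participation weights, or multiple imputation, built from HI, linked attendance, and hospital, perinatal and community data. Report the result beside the complete-case estimate, at least as a sensitivity analysis.
2. Do not make earlier AEDC results a required predictor. The census is triennial, with 2009, 2012 and 2015 available, so they are absent by design for most school-entry years. They also cannot predict participation in the AEDC itself.
3. In any component study where covariate loss proves material, use multiple imputation with the outcome in the imputation model.
4. Report the number and share of children lost at each step. Describe included against excluded children by standardised differences, and discuss them whatever the P value.

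The cost is extra analysis on data already linked and slightly wider intervals. The added analysis assumes missingness at random given the linked data, so bias remains if sitting depends on the unseen score. The report should say so.

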**Methods:**

Individual-level information linked across multiple administrative datasets will be used to conduct a series of retrospective observational studies on selected developmental and school outcomes. The predictor variables for all studies are the results from audiometric hearing assessments. The outcome measures are as follows: Australian Early Development Census results, representing developmental readiness for school, assessed around 5 years of age; Year 1 school attendance rates; Year 3 school-based academic performance, assessed in the National Assessment Program—Literacy and Numeracy; incidence of child maltreatment events (including both notifications and substantiated cases); and incidence of a first guilty verdict for youth offenders. Confounding and moderating factors available for the analysis include both community-level factors (including school fixed effects, socioeconomic status, level of remoteness, and housing crowdedness) and individual-level factors (including maternal and perinatal health and hospital admissions in early childhood).

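### Covariates are screened at univariate P<.25 with every two-way interaction tried, from a pool that can include variables on the pathway from hearing impairment to the outcome

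*Protocol article*

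**What the plan says.** All references are to the Protocol article. Under Statistical Analysis Plan, the component studies share one procedure. The stated aim is that "a parsimonious model building strategy will be adopted in the regression modeling process". The first step is: "Univariate regression analysis will first be carried out to select variables with" a P value below .25. The second is: "These and all possible 2-way interaction terms will be fitted in the multivariate regression" model-building process. There is one safeguard: "Variables deemed to be key confounders or moderators selected on the basis of past studies will be retained throughout the model-building process".

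Control Variables describes where the candidates come from: "Individual-level control variables will be retrieved from the linked health, education, child protection, and justice datasets". The same section adds a literature criterion: "We will draw reference from published literature in selecting control variables known to have confounding or moderating effects on the association being investigated". The Abstract gives examples of what is available: "individual-level factors (including maternal and perinatal health and hospital admissions in early childhood").

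The last part of Statistical Analysis Plan describes a separate path model for youth offending. It includes "indirect pathways by which AEDC outcomes, Year 1 school attendance, and Year 3 NAPLAN results act as mediators in the direct pathway". Child maltreatment also enters that model as a factor shaping offending, but is not among the mediators named in that sentence.

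**The concern.** The five hypotheses under Objectives ask whether HI is independently associated with each outcome, and the article presents the results as evidence on the impact of HI. Two features of the model-building rule work against that aim.

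First, a univariate screen measures association with the outcome, not causal role. A consequence of HI that also predicts the outcome passes as easily as a confounder does. Once it is in the model, the HI coefficient no longer includes the part of the effect that runs through it. A small adjusted coefficient could then be read as little impact, in work meant to guide policy and resource allocation.

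Timing in the data gives little protection. Under Dependent Variables, the first hearing test at any age stands for long-term hearing and may fall after the outcome. The test date therefore cannot show whether a covariate came before the hearing loss.

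Second, trying every pair of screened variables as an interaction makes chance findings likely. If an HI interaction is retained, the main HI coefficient holds only at the reference value of the other variable. HI has four categories, so each interaction with a binary or continuous covariate adds three coefficients. The usual P values also take no account of the search.

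**Working it through.** The article gives no candidate count, analysed sample size or retention threshold for this procedure, so there is no figure to reproduce. The numbers below are illustrations on stated assumptions.

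**1. What the pool can contain.** Set Control Variables beside the dataset descriptions under Outcome Measures:

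- Education: the data described are AEDC, attendance and NAPLAN (hypotheses 1 to 3). The path model treats all three as mediators between HI and offending.
- Child protection: maltreatment contacts (hypothesis 4).
- Justice: youth offending records (hypothesis 5).

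Nothing in either section excludes these from the component regressions, and nothing names them as covariates there. Age order limits the problem. AEDC is assessed at about 5 years, Year 1 attendance at 6-7 and NAPLAN at about 8, and offending follow-up starts at 10. School attendance and NAPLAN therefore cannot mediate the AEDC result. The exposed analyses are mainly attendance, NAPLAN, maltreatment at later ages and offending.

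**2. Interaction search.** Let k variables, counting HI, be in play. Pairs m = k(k-1)/2. With no true interactions and an assumed 5% level, expected false positives = 0.05m. With independent tests, P(at least one) = 1 - 0.95^m. Pairs that involve HI number k-1, and the chance of at least one false HI interaction is 1 - 0.95^(k-1).

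| k (assumed) | pairs | expected false positives | P(at least one) | HI pairs | P(at least one with HI) |
|---|---|---|---|---|---|
| 5 | 10 | 0.5 | 40% | 4 | 19% |
| 10 | 45 | 2.25 | 90% | 9 | 37% |
| 15 | 105 | 5.25 | 99.5% | 14 | 51% |
| 20 | 190 | 9.5 | about 100% | 19 | 62% |

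Most chance interactions would not involve HI. Those that do change the meaning of the main HI coefficient.

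**3. Adjusting for a mediator.** Let HI change the mediator by a, the mediator change the outcome by b per unit, and the direct effect be c. The total effect is c + ab; with the mediator in the model the HI coefficient estimates c. A simulation assumed n = 1000, binary HI at 50%, unit residual SDs, no shared unmeasured cause of mediator and outcome, and 1000 replicates per setting:

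| a, b, c (assumed) | total c + ab | estimate without mediator | estimate with mediator | significant at 5%, without → with |
|---|---|---|---|---|
| -0.3, 0.5, -0.15 | -0.30 | -0.297 | -0.146 | 99% → 61% |
| -0.3, 0.5, 0 | -0.15 | -0.150 | 0.001 | 57% → 4% |
| -0.2, 0.4, -0.12 | -0.20 | -0.198 | -0.119 | 82% → 47% |
| -0.5, 0.5, -0.05 | -0.30 | -0.300 | -0.049 | 99% → 12% |

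The mediator passed the P<.25 screen in every run of all four settings. The share of the total effect removed is ab/(c + ab): 50%, 100%, 40% and 83%.

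**4. A confounder missed by the screen.** In a case constructed so that the confounder's marginal association with the outcome is near zero, the screen dropped it in 76% of runs. Without it, the HI estimate was -0.249 against a true -0.30.

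**The case against.** The strongest reply is that selection is not by P value alone. Controls are to be guided by literature on confounding and moderation, and key ones stay in whatever the screen shows. That largely answers step 4: a confounder known from past work cannot be lost, so only unrecognised ones remain at risk. It does not answer step 3. Both safeguards keep variables in; neither keeps pathway variables out. The Introduction itself notes a large literature correlating maltreatment, offending, development, school performance and attendance, so literature guidance could put forward such variables.

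A reader might infer that the component models will adjust for AEDC, attendance, NAPLAN or maltreatment. The documents do not support that. No section lists them as covariates, the Abstract's examples are maternal, perinatal and hospital factors, and the path model shows that the authors recognise the mediating role. Figure 1 may assign further roles; it could not be seen here, and nothing in this point rests on it. What stands is that the stated rule permits such adjustment.

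A reader might also infer that several spurious interactions will end up in the final models. That too goes beyond the text. Interactions are candidates in a process meant to be parsimonious, and the retention rule is not given. Moderation is a declared interest, so examining some interactions is reasonable. The objection is to searching all of them.

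Finally, a condensed article may leave per-study covariate lists to a fuller plan. That is fair, and the absence of such lists is not the complaint. The screen and the all-pairs search are rules that the article does state.

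**Conclusion.** The point holds as a weakness in a stated rule. A P<.25 screen followed by all two-way interactions cannot separate confounders from consequences of HI, and the permitted source datasets hold the study's own outcomes. The risk to the HI estimate falls mainly on attendance, NAPLAN, maltreatment at later ages and offending. There, a mediator-adjusted coefficient is a partial effect and could understate the impact of HI. In the assumed settings the loss ran from 40% to all of the total effect. That size depends on the chosen path values and on a mediator actually being entered.

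For interactions, about 2, 5 or 10 chance findings are expected with 10, 15 or 20 screened variables at an assumed 5% level; the number retained is unknown. The change is worth making, but the article does not show that any component analysis is already compromised.

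**What to change.** Replace the P<.25 screen with one prespecified adjustment set per outcome, justified on causal grounds and fitted as specified. Suitable members are maternal and perinatal factors, sex, birth year and community factors, plus early-childhood hospital admissions where they are judged to be confounders. Keep the planned school fixed effects for attendance and NAPLAN.

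State that AEDC, attendance, NAPLAN, maltreatment and offending are not controls in the primary component models. Reserve them for the path model or for a secondary analysis labelled as estimating a partial effect.

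Name a few HI-by-moderator interactions in advance and report them as secondary. With 1 to 3 such terms, the expected number of false positives at 5% is 0.05 to 0.15.

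This changes wording in the analysis plan and needs no new data. The cost is a small loss of precision from covariates that may prove unnecessary.
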